#### A2 - Survey to document implementation activities

The survey of participants also contains questions on the actual implementation activities. We intend to record the extent to which the target group used the offered interventions and adaptions on it in the delivery phase of the implementation programs. Table 2 shows the frame of the questionnaire used in all studies to document implementation activities. The design of the questionnaire is based on a published framework [15], which distinguishes four aspects of intervention fidelity:

1. Content - Was the content of the intervention delivered as planned?

2. Duration - Was the intervention fully implemented across the intended time period?

3. Frequency - Was the intervention conducted as frequent as planned?

4. Coverage - Was the intervention applied to all individuals in the targeted group?

**Table 2 T2:** Questionnaire to document implementation activities (A2)

	**Yes**	**Partly**	**No**
**Intervention component 1:** Please describe the intervention component in sufficient detail (specify content, duration, frequency, coverage if applicable)			
Did you use this item as described in terms of duration? (if applicable)	□	□	□
Did you use this item as described in terms of frequency? (if applicable)	□	□	□
Did you use this item as described in terms of coverage? (if applicable)	□	□	□
Did you find this item helpful for the implementation of the recommendation/to reach the targets?	□	□	□
Did you adapt the content or format of this item in any way? If yes, please specify below!	□	□	□
**Intervention component 2:** Please describe the intervention component in sufficient detail (specify content, duration, frequency, coverage if applicable)			
…	□	□	□
Comments:			
Free text field: Can you think of other intervention components which might have been more helpful in order to improve the implementation of the recommendations/to reach the targets?			

For each implementation program the core components will be specified. For each core component, content, duration, frequency and coverage will be recorded in a structured way (Table 2). The content of the items will be specific for the different trials. A free text field is added to identify strategies that have been missed in the tailoring process so far, allowing the evaluation of the methods used for tailoring.

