### Data analysis

We will use the following analytical approach to answer the research questions addressed by this process evaluation:

1. Research question 1 - To what extent did the practitioners or patients use the various components of the planned intervention programs? and

2. Research question 2 - What is the validity of the methods used to tailor the implementation program to determinants of practice?In order to answer these questions a descriptive analysis of qualitative and quantitative data will be done separately in each country. The descriptive analysis of questionnaires will result in tables with frequency distributions. The qualitative interviews will be transcribed verbatim in the original languages. An iterative thematic analysis will be done, involving two or more researchers in order to identify key themes relevant for implementation.

3. Research question 3 - Which factors are associated with implementation of evidence-based practice in chronic illness care, after use of a tailored implementation program?

To answer this research question a summary outcome measure will be constructed in each trial, expressing professional performance by aggregating items reflecting implementation of evidence-based recommendations. This outcome will be standardized and taken as dependent variable in a regression analysis approach. The independent variables in this model will be a limited number of questionnaire items (to reduce chance capitalization), selected according to hypothesis informed by relevant key themes of the interviews. A special focus will be given to the association between professional performance and the questionnaire items concerning the application and adaption of the implementation program by the target group.

4. Research question 4 - How consistent are the findings across the trials?

A meta-analysis of quantitative and a meta-ethnography of qualitative data from all five studies will be conducted.

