A qualitative meta-ethnography will be conducted using the data from the interviews. For this purpose a description of subcategories with significant quotations from all studies will be provided in English. This material will be analyzed according to the principles of Noblit and Hare’s reciprocal translational analysis, which is recommended to be used when analyzing studies with similar topics [17,18]. The result of this analysis will be a set of key themes relevant in all studies. Interviews will be re-analyzed to explore how each single study contributes to the overall key themes. In a last step third order interpretation across the key themes will be considered if supported by a ‘line of argument’ across all studies.

A quantitative meta-analysis will be conducted, focused on the summary outcome measure in each trial, using the predictors that are identified as result from the analysis for question 3. While the items composing this aggregate outcome obviously differ among the trials, the assumption is that the resulting measures are reasonably comparable to allow pooling. Based on hypotheses derived from phase 1 and 2, individual data and/or clustered data from all trials will be included in a meta-regression analysis. This last step will efficiently make use of the total number of cases included across all studies and the shared instruments as described in this protocol.

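### The pooled analysis takes its predictors from the question 3 results in the same trials and on the same outcome, which biases retained estimates away from zero and builds in some of the consistency it should test

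*Protocol article*

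**What the plan says.** All the relevant text is in the Data analysis section of the protocol article, unless another section is named.

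- **Question 3, outcome.** Each trial builds a summary score of professional performance. "This outcome will be standardized and taken as dependent variable in a regression analysis approach".
- **Question 3, candidates.** The independent variables are "a limited number of questionnaire items (to reduce chance capitalization"), and they are "selected according to hypothesis informed by relevant key themes of the interviews".
- **Question 4, pooled analysis.** The quantitative meta-analysis is "focused on the summary outcome measure in each trial", "using the predictors that are identified as result from the analysis for question 3".
- **Question 4, meta-regression.** Later in the same paragraph: "Based on hypotheses derived from phase 1 and 2, individual data and/or clustered data from all trials will be included in a meta-regression analysis".
- **Instruments.** The section on survey A2 gives a questionnaire frame common to the studies, but adds: "The content of the items will be specific for the different trials".
- **Trials.** The section on survey A1 excludes the Norwegian trial from the survey, so four of the five trials can supply questionnaire predictors.

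The article gives no rule for when a predictor counts as identified, no number of candidates, no sample size and no significance level for these analyses.

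**The concern.** The inputs to question 3 are described separately, as items chosen by hypothesis. The phrase about predictors identified as its result therefore most naturally refers to the output of that regression. If so, the same outcome in the same trials is used first to choose predictors and then to estimate their pooled associations.

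This has two consequences:

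- Predictors whose estimates happened to be large by chance are more likely to be carried forward, so the pooled estimates of retained predictors are biased away from zero.
- Question 4 asks whether findings agree from trial to trial. Factors with no association in question 3 drop out of the synthesis, so it cannot show them to be null or inconsistent. Part of the apparent agreement comes from the selection.

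Limiting the number of question 3 items reduces chance findings at that stage. It does nothing about the step from question 3 to question 4. The Conclusions section concedes limited power, and selection exaggerates estimates most when power is low.

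The paragraph also names two bases for the pooled work without connecting them. If phases 1 and 2 are the tailoring phases described under Methods, hypotheses from them predate any trial outcome. Question 3 results do not.

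**Working it through.** **No figure to reproduce.** The article states no error rate, power, effect size, sample size or number of candidates for this analysis. What follows is an illustration, and every numerical input except the number of trials is an assumption.

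**Inputs**
- Trials: T = 4 (five minus Norway, from the section on survey A1), taken as equal in size.
- Units (professionals) per trial: n = 20, 40 or 80 (assumed); clustering ignored.
- Common true association ρ = 0, 0.1 or 0.2 (assumed).
- Trial estimate: normal around ρ with SE = 1/√(n−3). This gives 1/√17 = 0.243, 1/√37 = 0.164 and 1/√77 = 0.114.
- Identified: two-sided p<0.05 in at least one trial (assumed).
- Pooled estimate: mean of the four trial estimates, with standard error SE/√4.
- 400,000 replicates per setting.

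**Null predictors (ρ = 0)**
1. Chance of being identified: 1 − 0.95⁴ = 0.185 (simulated 0.185 to 0.186).
2. Chance of being identified and also significant in the pool: 0.032 (simulated).
3. Chance of being significant in the pool, given identified: 0.032/0.185 = 0.17, against 0.05 for a predictor pooled regardless of its result.
4. Mean absolute pooled estimate, identified against all:

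| n | Identified | All | Ratio |
|---|---|---|---|
| 20 | 0.149 | 0.097 | 1.5 |
| 40 | 0.101 | 0.066 | 1.5 |
| 80 | 0.070 | 0.046 | 1.5 |

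**True associations: mean pooled estimate after identification**

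| n | ρ = 0.10 | Excess | ρ = 0.20 | Excess |
|---|---|---|---|---|
| 20 | 0.175 | 0.075 | 0.275 | 0.075 |
| 40 | 0.155 | 0.055 | 0.235 | 0.035 |
| 80 | 0.134 | 0.034 | 0.210 | 0.010 |

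The excess shrinks as trials grow, because identification then depends less on chance.

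**Error rate per original candidate.** Step 2 gives 3.2%, which is below 5%. For K independent null candidates, the chance of at least one false pooled predictor is 1 − (1 − 0.032)^K with selection and 1 − 0.95^K when all are pooled without adjustment:

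| K | With selection | All pooled, unadjusted |
|---|---|---|
| 5 | 15% | 22.6% |
| 10 | 28% | 40.1% |
| 20 | 48% | 64.2% |

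Selection therefore raises the error rate among the predictors that are reported, not the rate per candidate examined.

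**After the fix.** With a fixed list pooled whatever the question 3 result, each null predictor is significant 5.0% of the time and there is no selection bias. Multiplicity remains. A Bonferroni threshold of 0.05/K brings the familywise rate to about 4.9% for K from 3 to 20.

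**The case against.** The strongest reply is that the inflation depends on a rule the article never states. It mentions no p-value threshold and no stepwise procedure, and it says that question 3 items are few and chosen by hypothesis. If the identified predictors are simply those specified for the question 3 model, there is no selection on the outcome and no bias. That reading is possible. It fits the wording less well, because the choice of inputs is described elsewhere and in other terms. It is a reason to clarify the sentence, not to leave it as it is.

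Second, the analysis is exploratory, promises no error rate and admits limited power. This stands. It lowers the weight of the point but does not remove the bias in the retained estimates.

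Third, the two bases may be two steps: a meta-analysis of question 3 predictors, followed by a meta-regression on earlier hypotheses. This also stands. The text leaves the link unexplained, and does not show that the two bases are incompatible.

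Fourth, choosing predictors from interview themes is a legitimate mixed-methods design and is not selection on the regression outcome. Agreed; the concern does not extend to it.

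A reader might also infer that a predictor would be pooled only over the trials in which it came out positive, since survey items are trial-specific. That would distort far more: under the same assumptions, a true 0.20 would average about 0.42 at n = 40. The article does not support this, because it says "individual data and/or clustered data from all trials will be included in a meta-regression analysis".

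**Conclusion.** The point holds in a conditional form. On the plain reading, question 3 findings decide what is pooled for question 4, on the same outcome and in the same trials. Retained estimates are then biased away from zero, and consistency is partly built in. The relation to the phase 1 and 2 hypotheses is left open.

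The size cannot be derived from the article. Under the assumed rule, pooled significance among retained null predictors is about 17% instead of 5%, and the excess on true associations of 0.10 to 0.20 lies between about 0.01 and 0.08 for 80 down to 20 units per trial.

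Two stronger conclusions might be drawn and are not supported. One is that the plan raises the number of false positives: per candidate it does not (3.2%), and unadjusted pooling of every candidate would produce more of them. The other is that only question 3 findings are pooled and that the results are certainly inflated: the article does not say only, and the inflation depends on what identified means. This is a cheap improvement to an exploratory analysis.

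**What to change.** Replace the clause on the pooled predictors with wording such as:

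> using all predictors specified for the question 3 models, as one common list fixed before process data are linked to outcomes; every trial with survey data reports every coefficient that its instruments allow, and all are pooled whatever the question 3 result

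Also state how the phase 1 and 2 hypotheses feed that list, and label as exploratory any predictor added after question 3 results have been seen. Interview-informed predictors may stay on the list, provided that they are fixed before outcome linkage.

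The cost is a sentence or two of protocol text and a short dated list. The Trial status section says the work is still in planning, so this can be done in time. The downside is that some null predictors will also be pooled. The number of pooled tests should therefore be reported, or the significance threshold adjusted for it.

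### Question 4 pools the predictors that question 3 singled out, on the same outcome and trials, so the pooled associations and the consistency reading are distorted by selection

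*Protocol article*

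**What the plan says.** All of the relevant text is in the Data analysis section of the Protocol article.

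- **Question 3** is worded there as "Which factors are associated with implementation of evidence-based practice in chronic illness care, after use of a tailored implementation program". Each trial builds a summary measure of professional performance: "This outcome will be standardized and taken as dependent variable in a regression analysis approach". The independent variables are "a limited number of questionnaire items (to reduce chance capitalization), selected according to hypothesis informed by relevant key themes of the interviews".
- **Question 4** asks how consistent the findings are across trials. Its quantitative meta-analysis is "focused on the summary outcome measure in each trial", "using the predictors that are identified as result from the analysis for question 3".
- **A further basis** is named shortly afterwards: "Based on hypotheses derived from phase 1 and 2", "individual data and/or clustered data from all trials will be included in a meta-regression analysis".

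No hold-out sample, leave-one-trial-out step or adjustment for selection is described between questions 3 and 4. The survey that supplies the questionnaire items runs in four of the five trials, because the Norwegian trial does not conduct it (section A1).

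**The concern.** The guard against chance findings in question 3 limits which items enter the regressions. It does not cover the next step, where the results of those regressions decide which predictors are pooled. If a predictor goes forward because it stood out in one or more trials, the chance excess in those trials goes with it into the pooled estimate.

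Two consequences bear directly on question 4. The pooled associations that readers see will be too large on average. The trial that brought a predictor in will also tend to look different from the others, even when the true association is identical everywhere, so an analysis meant to judge consistency will suggest inconsistency that selection created. In addition, a weak association shared by all trials may be flagged in none of them and so never be pooled.

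**Working it through.** The article states no threshold, item count, sample size or power figure, so there is no figure of the plan's own to reproduce. The check has two parts.

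**1. Do selection and pooling share data?** Question 3 uses the standardized summary outcome of each trial. Question 4 uses the summary outcome of each trial, with data from all trials. Outcome and trials are the same, and no separate sample is named. They do share data.

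**2. What would selection do?**

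Assumptions, none of them from the article except the number of trials:
- four trials (those with the survey), of equal size, with the same true association in each;
- independent normal estimates and fixed-effect pooling;
- a predictor is carried forward if two-sided p<0.05 in at least one trial.

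Formulas: with z-statistics z1 to z4, the pooled statistic is (z1+z2+z3+z4)/√4. Heterogeneity is Cochran's Q on 3 degrees of freedom, tested at 0.10.

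*No true association*
- Chance of being carried forward: 1 − 0.95⁴ = 0.185.
- By simulation, given carry-forward: pooled test significant at 5% in 17%; Q significant in 43%.
- With no filter: 5% and 10%, the nominal rates.
- Counted over all candidates: 0.186 × 0.173 = 0.032, i.e. 3.2% of null items are both carried forward and significant when pooled. This is below 5%.

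*True slope 0.10, standard error 0.13 per trial*
- Pooled standard error: 0.13/√4 = 0.065. Expected pooled z: 0.10/0.065 = 1.54.
- Chance of a pooled finding with no filter: P(Z > 1.96 − 1.54) ≈ 0.34.
- Chance of being carried forward and then significant: 0.25 (simulated).
- Mean pooled slope given carry-forward: 0.141, i.e. 0.141/0.10 = 1.41, or 41% too large.

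*Sensitivity to sample size and effect.* Mean pooled Fisher z under the same any-trial rule:

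| True value | n=20 per trial | n=40 | n=100 |
|---|---|---|---|
| 0.100 | 0.174 (+74%) | 0.156 (+56%) | 0.128 (+28%) |
| 0.203 | 0.278 (+37%) | 0.237 (+17%) | 0.208 (+2%) |

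*Sensitivity to the rule* (null items, given carry-forward). With p<0.10 in any trial, the pooled test rejects in about 13%. With p<0.05 in at least two trials, it rejects in 34–36% and Q in 75–78%.

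*What removes it.* When all candidates are pooled, null rejection is 4.9–5.1% and Q rejects in about 10%. When one given trial selects and only the other three are pooled, null rejection is 4.6–5.4%, against 17.7–19.2% if the selecting trial stays in.

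**The case against.** The strongest reply is that the article states no significance filter. The only explicit selection rule is the one for question 3 items, which are "selected according to hypothesis informed by relevant key themes of the interviews". A predictor identified by question 3 could simply be any item on that list. If the whole list goes forward whatever its results, there is no selection bias. This stands as a limit on certainty. But the sentence ties the predictors to the result of an analysis that asks which factors are associated, and the more natural reading is that association decides.

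A second reply is that the work is exploratory, with heterogeneity and suboptimal power admitted in the Conclusions, and that question 4 takes question 3 findings as its input by design. That is fair, and no confirmatory claim is made. But low power makes the overestimation larger, and an exploratory consistency assessment is still misled by heterogeneity that selection created.

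Two stronger readings are tempting and are not supported:

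- **That the plan inflates the false-positive rate outright.** The 17% applies only to items already selected. Per candidate item the rate is about 3%, lower than with no filter. Nor does the share of false findings rise: with equal numbers of null and true items it is 0.05/(0.05+0.337) = 13% without the filter and 0.032/(0.032+0.246) = 12% with it.
- **That the article contradicts itself by naming two sources of predictors.** The sentence on phases 1 and 2 can be read as a separate, later meta-regression step. The relation between the two lists is unclear, but a contradiction is not shown.

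The point is also not a complaint about detail left to an analysis plan. The article states a carry-forward rule, and an analysis plan that followed it would inherit the problem.

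**Conclusion.** The concern holds in a conditional form. As worded, the question 4 meta-analysis most naturally pools predictors chosen by their observed association, on the same outcome and trials. Given that selection, pooled associations are overestimated and the heterogeneity reading is distorted.

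The direction follows from the design, but the size cannot be derived from the article. Under the any-trial p<0.05 rule with four equal trials, overestimation runs from about 2% to 74% over the sample sizes and effects tried, and spurious heterogeneity among selected null items is about 43% instead of 10%. These figures rest on the assumed rule, equal trials, independent normal estimates and a common true association. If every question 3 item is in fact carried forward, the distortion disappears.

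**What to change.** Replace the clause that takes predictors from the question 3 results with wording such as: *Every item entered in the question 3 models, and any further item listed from the logic models or the phase hypotheses, will be pooled from every trial that measured it, whatever its question 3 result.*

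Add one sentence saying how this list relates to the phase 1 and 2 hypotheses named for the meta-regression: the same list, a subset, or a separate step. Label as exploratory any predictor added because of its question 3 result. For such predictors, a pooled estimate with the discovery trial left out is an optional sensitivity analysis. It costs precision with only four survey trials, so it need not be the main estimate.

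The cost is small. The article's Trial status section says the work is still being planned, and the data would be collected anyway. A few more coefficients are pooled, and some findings carry an exploratory label.

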## Conclusions

Process evaluation is essential to understand the effects and to explore potential causal mechanisms of complex interventions. The planned process evaluation in the TICD project needs to find a balance between standardization of methods across trials and adaptation of measures to the specific characteristics of each trial. Despite obvious limitations, such as heterogeneity and suboptimal statistical power, we believe that the planned study will contribute to our knowledge on determinants of change in chronic illness care and methods for tailoring implementation programs to barriers and facilitators of change.

## Trial status

The trial is currently in the planning phase.

